### Outcome measures

The primary outcome is the severity of depressive symptoms during the year following the intervention relative to baseline. Depressive symptoms are repeatedly assessed with the IDS-SR. Mixed effects regression analysis will estimate the integrated treatment effect on all four follow-up IDS-SR assessments from T1 (7 weeks, directly after the six-week intervention) to T4 (52 weeks), relative to T0 (baseline).

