### Sample size calculation

Sample size calculations for mixed effect regression models require a number of estimates, or assumptions [61]. We estimate an average dropout of 3% with every next assessment (all-completers at T0, 3% drop-out at T1 to 12% drop-out at T4). We estimate the (within-subject) intraclass correlation coefficient (ICC) of the pre-assessment and four follow-up assessments to be approximately 0.50. A somewhat higher ICC will slightly inflate the minimal detectable effects, a somewhat lower ICC will slightly lower the minimal detectable effects. In the two by two factorial intervention design, the ratio of participants who will receive CBT-I versus those who will not is 1. This is also the case for those who will receive CT versus those who will not. For the interaction effect of CBT-I x CT, the ratio of participants who will receive both interventions versus those who will not is 1/3. We follow Cohen’s suggestion that an effect size below *d* = 0.2 (small) is not likely to be clinically significant, that *d* = 0.5 represents a medium effect size, and that *d* = 0.8 represents a large effect size [62]. A feasible total number of completers (i.e. complete data on the ambulatory recordings, EEG sleep recordings, MRI and questionnaires) at baseline is *N* = 120, *N* = 30 for each of the four groups, of whom we assume that *N* = 26 per group will complete all follow-up assessments. At a significance threshold of *α*  = 0.05, this sample size provides a power 1-*β*  = 0.80, the minimal detectable interaction effect is *d* = 0.5, while the minimal detectable main effects of either CBT-I or CT are *d* = 0.44 (medium). A previous similar study reported a more than medium effect of CBT-I on depressive symptoms at T1 (*d* = 0.74) up to a large effect at T4 (*d* = 1.12) [63].

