### Statistical analyses

Statistical analyses aim at determining the relative efficacy of internet-guided CBT-I, CT treatments and their combination, for the prevention of worsening of depressive symptoms in people with the type of ID that heralds increased risk of developing depression. The long-term effects of interventions and their interactions on depressive symptoms and on the probability to develop a diagnosis of depression will be estimated with mixed effect linear and logistic regression models using R [45].

In order to allow for an intention-to-treat analysis including all available data while accounting for a possibly variable number of missing data, hierarchical mixed effect linear and logistic regression models will be employed. Regressors are a random intercept, time, dummy-coded assignment to CBT (yes = 1, no = 0) and CT (yes = 1, no = 0) and a dummy coded variable indicating follow-up (T1-T4 = 1) versus baseline (T0 = 0). The interaction effect estimates of interest are CBT by follow-up, CT by follow-up and CBT-I by CT by follow-up [64]. The time variable estimates linear changes over time. Ancillary analyses will evaluate treatment by time effects (i.e., treatment effects changing linearly over time). Linear mixed effect models will also be used evaluate secondary outcomes (insomnia severity, cost-effectiveness, brain function and structure). A logistic mixed effect model will be used to evaluate the secondary outcome of a diagnosis of depression at T4. We will explore the effect of various variables, including the number of previous depressive episodes, time since last depressive episode, and expectation of intervention effectiveness.

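### The primary model's only random term is an intercept, so its 5% level depends on baseline correlating with follow-ups exactly as follow-ups correlate with each other, which the protocol does not support

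*Protocol article*

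**What the plan says.** The Outcome measures section defines the primary effect as an integrated effect over the four follow-up IDS-SR assessments relative to baseline. The Statistical analyses section implements this with T0 kept as an outcome row: "Regressors are a random intercept, time, dummy-coded assignment to CBT" and CT, together with "a dummy coded variable indicating follow-up (T1-T4 = 1) versus baseline (T0 = 0"). The tests follow from that coding: "The interaction effect estimates of interest are CBT by follow-up, CT by follow-up and CBT-I by CT by follow-up". The intercept is the only random term named. There is no random slope, random follow-up effect, residual correlation, unstructured covariance or robust standard error.

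The Sample size calculation section makes the matching assumption: "We estimate the (within-subject) intraclass correlation coefficient (ICC) of the pre-assessment and four follow-up assessments to be approximately 0.50". The two sections agree with each other. Both treat T0 as exchangeable with T1-T4 in its correlations, and neither gives a figure to support that.

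**The concern.** Each primary test compares, between arms, one T0 value with the average of T1-T4. Under a random intercept, the variance of that change is built from one pooled residual variance and one ICC. T0, however, is the only assessment before the six-week intervention period, and the other four all come after it. If people change by different amounts after T0 and partly keep that change, their follow-ups will be more alike than any of them is to baseline. The model then treats the four follow-ups as more independent information on change than they are.

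At stake is the 5% level of all three primary tests, and with it the chance of a false claim that treating insomnia prevents worsening of depressive symptoms.

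**Working it through.** **Inputs from the protocol article.** Single ICC 0.50, 30 per group with 26 completing, 3% dropout per assessment, α = 0.05 and power 0.80 (Sample size calculation); visits at weeks 0, 7, 26, 39 and 52 (Assessment points and measures). Sidedness is not stated, so two-sided is used.

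**Assumed, not in the document.** Separate correlations: r_bf (baseline with follow-up) and r_ff (between follow-ups).

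**1. The plan's own figures.** At ICC 0.50 the variance of the mean of four follow-ups is (1 + 3 × 0.5)/4 = 0.625. For change from baseline it is (1 − 0.5)(1 + 1/4) = 0.625, the same.
- Main effect, 52 v 52: 2.80 × √(0.625 × 2/52) = 0.434 (0.439 with t quantiles); stated 0.44.
- Interaction at the stated 1/3 ratio, 26 v 78: 2.80 × √(0.625 × (1/26 + 1/78)) = 0.502; stated 0.5.

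The planning figures are thus reproduced with one common correlation.

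**2. True against model variance of mean(T1-T4) − T0, unit variances.**
- True: 1 + (1 + 3r_ff)/4 − 2r_bf.
- Random-intercept model: 1.25 × (1 − r̄). Of the ten visit pairs, four involve T0 and six do not, so r̄ = 0.4r_bf + 0.6r_ff.
- Difference: 1.5 × (r_ff − r_bf).

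With equal variances, the standard error is too small exactly when r_ff exceeds r_bf.

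**3. Type I error at nominal 5%**, as 2Φ(−1.96/k), with k = √(true/model). The last column is a simulation of the planned factorial model fitted by REML: 4,000 null trials per scenario, N = 120, actual visit weeks, stated dropout. It gives the range over the three interaction terms.

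| r_bf / r_ff | True | Model | k | Type I error | Simulated |
|---|---|---|---|---|---|
| 0.50 / 0.50 | 0.625 | 0.625 | 1.00 | 5.0% | 4.9-5.4% |
| 0.50 / 0.60 | 0.700 | 0.550 | 1.13 | 8.2% | 7.5-8.7% |
| 0.40 / 0.60 | 0.900 | 0.600 | 1.22 | 11.0% | not run |
| 0.35 / 0.60 | 1.000 | 0.625 | 1.26 | 12.1% | 11.4-12.0% |
| 0.50 / 0.70 | 0.775 | 0.475 | 1.28 | 12.5% | 12.4-12.5% |
| 0.60 / 0.50 | 0.425 | 0.575 | 0.86 | 2.3% | about 2.2% |

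The linear time term is common to all arms and does not remove the effect. Nor does an average correlation of exactly 0.50: r̄ is 0.4 × 0.35 + 0.6 × 0.60 = 0.50 in the fourth row.

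**4. Smooth decay with time.** The mean lag is (7 + 26 + 39 + 52)/4 = 31 weeks for baseline pairs and (19 + 32 + 45 + 13 + 26 + 13)/6 = 24.7 weeks for follow-up pairs. Decay therefore opens only a small gap. Exponential decay with average correlation 0.50 gives mean r_bf 0.466 and r_ff 0.523, true 0.710 against model 0.625, and 6.6%. Varying the form of the decay gives about 6-7.5%.

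**5. Differing individual change.** Start from ICC 0.50 and add a person-level shift to T1-T4 with variance s, as a fraction of baseline variance (assumed). The true variance is 0.625 + s. The model variance is 0.625 + s/4, because the shift adds 0.8s to the mean variance and 0.6s to the mean covariance, and 1.25 × 0.2s = s/4. Type I error is 6.3% at s = 0.10, 8.2% at s = 0.25 and 11.0% at s = 0.50.

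**6. Reduced T0 variance from selection.** With T0 variance cut to 0.64 and covariances adjusted for range restriction, 0.50/0.50 gives true 0.535 against model 0.603, or about 3.8%. From 0.50/0.60, the 8.2% falls to about 6.8%. The amount of selection is assumed.

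**The case against.** The strongest reply is that nothing in the article establishes the condition. It gives one ICC, its model agrees with that ICC, and the reverse ordering makes the test conservative. This stands. A reader might infer that the three standard errors simply are too small; the documents do not show that, because they give no separate correlations.

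A reader might also take the exclusion of current major depressive disorder as further support, since it narrows the spread at T0. It points the other way: step 6 shows that smaller T0 variance offsets the inflation and can make the test conservative.

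Differing response to treatment is not a complete mechanism either. If treatment does nothing to anyone, it creates no response differences. Inflation under the null needs people to differ in natural course after T0, or treatment effects that vary between people but average to zero. Both are possible; neither is documented. The visit schedule by itself supports only the mild case in step 4.

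Finally, a condensed article may leave residual covariance and degrees of freedom to an analysis plan. That answers an omission. Here, however, the article lists the model's terms and names one random term, so the point concerns what it states.

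**Conclusion.** The point holds in conditional form. The stated primary model keeps its 5% level only if baseline correlates with follow-ups as they correlate with each other (or if departures happen to cancel), and the article offers no evidence for this. With equal variances, plausible departures run from about 6-7.5% (smooth decay) to about 8% (0.50/0.60). The 11-12.5% figures need correlation gaps of 0.20 to 0.25, which no figure in the article supports. A smaller T0 variance or the reverse ordering lowers these values, possibly below 5%. All percentages rest on assumed correlations; the algebraic result that the variance error equals 1.5 × (r_ff − r_bf) needs only equal variances. This is an inexpensive improvement to a stated specification, not a demonstrated error in the planned result.

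**What to change.** Keep the fixed effects, the three treatment-by-follow-up estimates and the estimand as planned. Replace the random-intercept covariance with an unstructured within-person covariance over T0-T4 (5 variances + 10 covariances = 15 parameters, for 120 participants), with Kenward-Roger or Satterthwaite degrees of freedom. If that fails to converge, add a person-level random follow-up effect, correlated with the random intercept, or keep the random intercept and report cluster-robust standard errors. Name the fallback order in advance.

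Both the unstructured form and the random follow-up effect contain the present model as a special case. If the common ICC is right, the loss is a few degrees of freedom; otherwise the cost is one line of specification and slightly more computing. No data collection changes. Because the Blinding section has analysts work on coded conditions, the line can be fixed before allocation is revealed.

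### As coded, the CBT and CT terms compare a single arm with treatment as usual, not the main effects the trial was sized for, so power at d = 0.44 is about 52% rather than 80%

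*Protocol article*

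**What the plan says.** Under Sample size calculation, the protocol article describes the comparison behind each main effect: "the ratio of participants who will receive CBT-I versus those who will not is 1", and it says the same of CT. With 26 completers in each of four arms, that is 52 against 52. The effect it claims to detect with 80% power at a 0.05 threshold is given as "while the minimal detectable main effects of either CBT-I or CT are" d = 0.44.

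Under Statistical analyses, the mixed model has a random intercept, time, a 0/1 indicator separating the follow-ups T1 to T4 from baseline, and treatment entered as "dummy-coded assignment to CBT (yes = 1, no = 0) and CT (yes = 1, no = 0". The targets are then named in one sentence: "The interaction effect estimates of interest are CBT by follow-up, CT by follow-up and CBT-I by CT by follow-up".

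The section gives no centred coding and no marginal contrast. It has no step in which the three-way term is dropped before the two-way terms are read.

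**The concern.** What a two-way coefficient means depends on the coding once a three-way product is in the model. With 0/1 dummies, the CBT by follow-up coefficient is the effect of CBT-I where CT equals 0, which is the CBT-I arm against the treatment-as-usual arm. The CT by follow-up coefficient is likewise the CT arm against treatment as usual. The combination arm does not count as a CBT-I arm, and the CT arm does not count as a comparator for CBT-I.

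Two things are at stake. First, the tests as written lose the factorial efficiency on which N = 120 rests, so the stated d = 0.44 does not belong to them. Second, the coefficients could be read as main effects when they are simple effects. The two differ whenever the treatments interact, and interaction is one of the trial's own questions.

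**Working it through.** **Inputs, all from Sample size calculation unless noted**

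- 26 completers per arm (30 randomised).
- "intraclass correlation coefficient (ICC) of the pre-assessment and four follow-up assessments to be approximately 0.50".
- Threshold 0.05 and power 0.80. Sidedness is not stated. Two-sided is assumed because it reproduces the plan's figure, whereas one-sided would give 0.386. The multiplier is 1.96 + 0.84 = 2.80.
- 0/1 coding and the three named terms, from Statistical analyses.

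**Step 1. Variance factor.** The change from baseline to the mean of four follow-ups has variance, in units of the outcome SD squared, (1 - 0.5) × (1 + 1/4) = 0.625. The mean of the four follow-ups alone gives the same value at this ICC: (1 + 3 × 0.5)/4 = 0.625.

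**Step 2. Reproduce the plan's figure (52 against 52).**

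- SE = sqrt(0.625 × 2/52) = 0.155.
- Minimal detectable d = 2.80 × 0.155 = 0.434 (0.439 with the t distribution).
- Power at 0.44 = Φ(0.44/0.155 - 1.96) = 81% (80.3% with t).

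The stated 0.44 therefore belongs to the two-arms-against-two-arms comparison. The same variance also returns the stated interaction figure when applied to the split the plan describes, 26 against 78: d = 0.502. This supports the inputs. Whether that split is the right contrast for an interaction is a separate matter.

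**Step 3. The coefficient as coded.** Write b1 for CBT by follow-up and b3 for the three-way term. The CBT-I effect is b1 when CT = 0 and b1 + b3 when CT = 1. The factorial main effect is the average, b1 + 0.5 × b3. The coefficient b1 alone is 26 against 26:

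- SE = sqrt(0.625 × 2/26) = 0.219.
- Minimal detectable d = 2.80 × 0.219 = 0.614.
- Power at 0.44 = Φ(0.44/0.219 - 1.96) = 51.9% (50% to 51% with t).

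The ratio of the two standard errors is √2 whatever the ICC.

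**Step 4. Check in the longitudinal model.** Generalised least squares with a random intercept, a linear time term and visits at weeks 0, 7, 26, 39 and 52 gives:

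| Model and data | 0/1 coding: SE, power at 0.44 | -0.5/+0.5 coding: SE, power at 0.44 |
|---|---|---|
| All lower-order terms, 26 per arm complete | 0.219, 52% | 0.155, 81% |
| All lower-order terms, 30 per arm, stated dropout | 0.208, 56% | 0.147, 85% |
| All lower-order terms, 30 per arm, no dropout | 0.204, 58% | 0.144, 86% |
| CBT × CT term omitted, 26 per arm complete | 0.196, 61% | 0.155, 81% |
| CBT × CT term omitted, 30 per arm, stated dropout | 0.187, 66% | 0.147, 85% |
| CBT × CT term omitted, 30 per arm, no dropout | 0.183, 67% | 0.144, 86% |
| No three-way term, 26 per arm complete | 0.155, 81% | 0.155, 81% |

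In the models with all lower-order terms, the standard error of the three-way coefficient is the same under both codings.

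A complete-data simulation (6,000 runs, within-subject equivalent of the random-intercept model, additive effects of 0.44) agrees. Power for the two treatments was 0.50 and 0.52 with 0/1 coding, and 0.80 and 0.81 with -0.5/+0.5 coding on the same data.

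**The case against.** **The single model is inferred.** The article prints no equation and does not list a CBT × CT term. If the two-way effects came from a model without the three-way product, 0/1 coding would do no harm and power would stay near 81%. This condition stands. However, one sentence names all three terms as the targets of the model just described, and nothing indicates a second fit.

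**The figure of 52% is a completer calculation.** The plan intends to use all available data, and the literal list of regressors lacks the CBT × CT term. This stands as a matter of precision: the range is about 50% to 67%. In the model without that term it is also not strictly true that the other two arms contribute nothing. A model constraining baseline means to be equal would reach about 74% to 77% (26 complete, or 30 with dropout), but the plan lists CBT and CT as regressors, so that is not the stated model.

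**Comparison with treatment as usual may be what is wanted.** The Research design section describes the trial as comparing CBT-I, CT and their combination against treatment as usual, which fits the 0/1 coefficients. In that case the analysis is as intended and the sample size statement is wrong. The mismatch remains, and only the place of the correction changes.

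**Main effects are not always better powered.** The gain assumes additive effects. Suppose each treatment alone gives 0.44 and the combination adds nothing further. The average main effect is then (0.44 + 0)/2 = 0.22, with power Φ(0.22/0.155 - 1.96), about 29%, below 52%. This stands, and it is why simple effects should be shown alongside.

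**The shortfall applies at the stated minimum.** At d = 0.74, which the article cites for CBT-I from an earlier study, the single-arm comparison has Φ(0.74/0.219 - 1.96), about 92%. That is correct, but the article cites no such effect for CT, and 0.44 is the sensitivity it claims for both.

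**Coding is only a reparametrisation.** With all lower-order terms present the fit is identical and the marginal effect can be derived from it. That is true, but the article names the coefficients themselves as the estimates of interest.

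**Conclusion.** The concern holds. The sample size section and the analysis section describe different contrasts, and the stated 80% power at d = 0.44 belongs to one that the written analysis does not test. On the plan's own basis the coded coefficients have a minimal detectable effect of about 0.61 and power of about 52% at 0.44. Every version that keeps the listed regressors and the three-way term stays at or below 67%.

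This rests on all three terms being in one model, two-sided testing, ICC 0.50, and a single-treatment effect of 0.44 with no interaction. It is a fault in what the article states, not something left to a fuller analysis plan, because the article itself fixes both the coding and the terms of interest.

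**What to change.** State which contrast is primary, then align coding and sizing before the data are analysed.

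- **If factorial main effects are primary, as the sample size section implies:** code CBT and CT as -0.5/+0.5, keep follow-up as 0/1, and include all lower-order terms. Equivalently, keep 0/1 and pre-specify the marginal contrasts: the two-way coefficient plus half the three-way coefficient. The three-way coefficient remains the difference of differences. Report each arm against treatment as usual as secondary contrasts.
- **If arm-against-treatment-as-usual effects are primary:** keep 0/1 coding, say so, and restate the minimal detectable effect as about 0.61 (0.58 using all available data from 30 per arm with the stated dropout). Detecting 0.44 on that contrast would need 0.625 × 2 × (2.80/0.44)² = 50.6, so 51 completers per arm, about twice the planned 26.

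Either correction is a line of text and a line of analysis code, with no change to recruitment. The price of the first is that, if the treatments interact, the main effect is an average over the other treatment and must be read beside the simple effects.

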### Randomization

Participants of the RCT will be randomized to one of the four groups: CBT-I, CT, combination of CBT-I and CT, and treatment as usual (*N* = 30 for each group). Simple randomization will be applied until 2 to 4 participants have been randomized to each of the four groups. In order to ascertain balanced and equally sized groups across the intervention conditions, subsequent participants will be assigned according to covariate adaptive randomization [42]. Matching variables include age, sex, insomnia type, baseline severity of insomnia (ISI [37]) and depressive symptoms (Inventory of Depressive Symptoms – Self Report, IDS-SR [43]), use of sleep medication, suspected mild sleep disordered breathing, suspected mild restless leg syndrome, Body Mass Index (BMI), time of year at inclusion, and group size at inclusion. Since matching includes both continuous and categorical covariates, randomization will be done following the method proposed by Frane [44]. This method evaluates between-group differences for each of the covariates in case a new participant would be assigned to each of the treatment groups by obtaining *P* values from analysis of variance (ANOVA) for the continuous covariates and Chi-square tests for the categorical covariates. For each covariate, this procedure provides four *P* values, one for each possible group assignment. This smallest of all P values identifies the least desirable assignment. Of the four possible group assignments, the most desirable will be the one that maximizes the smallest *P* value across all covariates. This will be the final group assignment for that participant, because it keeps imbalance over groups as small as possible. The randomization is performed using R [45].

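### The primary model leaves baseline IDS-SR free by treatment factor although the allocation balances it, so the standard error is too wide and the test conservative

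*Protocol article*

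**What the plan says.** Under Outcome measures the protocol article states: "Mixed effects regression analysis will estimate the integrated treatment effect on all four follow-up IDS-SR assessments", relative to T0. Statistical analyses gives the regressors: a random intercept, linear time, 0/1 indicators for CBT and CT, and "a dummy coded variable indicating follow-up (T1-T4 = 1) versus baseline (T0 = 0". The effects of interest are CBT by follow-up, CT by follow-up and their three-way term. T0 is thus an outcome row, and CBT and CT also stand as terms of their own. Baseline IDS-SR is not a covariate.

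Under Randomization, after a short run of simple randomization, each participant goes to the group that maximizes the smallest imbalance P value over all covariates. "Matching variables include age, sex, insomnia type, baseline severity of insomnia" and, further on in the same sentence, baseline IDS-SR.

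Sample size calculation assumes an "intraclass correlation coefficient (ICC) of the pre-assessment and four follow-up assessments to be approximately 0.50", 30 per group at baseline and 26 completing all follow-ups. It concludes that at 80% power "the minimal detectable main effects of either CBT-I or CT are *d* = 0.44 (medium").

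**The concern.** A stand-alone treatment term next to a treatment-by-follow-up term lets the T0 mean differ by treatment. The interaction then compares change from baseline. This costs precision unless baseline and follow-up are almost perfectly correlated, and the plan assumes 0.50.

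The allocation adds a second problem. It forces the baseline IDS-SR means together, but the model's standard error is calculated as if baseline differences arose freely by chance. The reported uncertainty is then larger than the estimate's actual variability. At stake are intervals that are too wide, a test below its nominal level, and power lost in a trial whose size is set by feasibility.

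**Working it through.** Units are SDs of IDS-SR at one assessment. ρ is the ICC, taken as exchangeable in line with the random intercept. Figures are for the main effect of one factor, two-sided α = 0.05 (sidedness is not stated, but this reproduces the plan).

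**1. The plan's own figure.**
- Variance of the mean of four follow-ups: (1 + 3ρ)/4 = 0.625 at ρ = 0.50.
- With 52 v 52 completers: 2.802 × √(0.625 × 2/52) = 0.434 (0.439 with t quantiles). The stated 0.44 is reproduced; power at 0.44 is 0.81.
- Interaction with the stated 1:3 ratio: 2.802 × √(0.625 × (1/26 + 1/78)) = 0.502, against the stated 0.5.

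**2. The planned model.** Variance of follow-up mean minus baseline: (1 + 3ρ)/4 + 1 − 2ρ = 1.25(1 − ρ) = 0.625. At ρ = 0.50 this equals the variance in step 1, so the stated figure also fits the planned model.

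**3. Baseline constrained or conditioned on.** Variance: (1 + 3ρ)/4 − ρ² = 0.625 − 0.25 = 0.375.
- Reduction: 1 − 0.375/0.625 = 40%. Standard error ratio: √0.6 = 0.775.
- 52 v 52, allocation ignored: detectable effect 2.802 × √(0.375 × 2/52) = 0.336; power at 0.44 is 0.96.
- Generalized least squares with 30 per group and the stated dropout: standard error 0.147 to 0.115, detectable effect 0.41 to 0.32, power at 0.44 from 0.85 to 0.97.

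| Assumed ICC | Planned variance | Adjusted variance | SE ratio |
|---|---|---|---|
| 0.3 | 0.875 | 0.385 | 0.66 |
| 0.4 | 0.750 | 0.390 | 0.72 |
| 0.5 | 0.625 | 0.375 | 0.77 |
| 0.6 | 0.500 | 0.340 | 0.82 |
| 0.7 | 0.375 | 0.285 | 0.87 |
| 0.8 | 0.250 | 0.210 | 0.92 |

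**4. Effect of the allocation (60 v 60, no dropout).** The change-type estimate equals the adjusted estimate minus (1 − ρ) times the baseline difference. Its variance is 0.375 × 2/60 + 0.25 × Var(baseline difference).
- Unrestricted randomization: the baseline difference has SD √(2/60) = 0.183. The variance is 0.0125 + 0.25 × 0.0333 = 0.0208, so SE = 0.144. This is what the planned model reports.
- Simulated allocation: the baseline difference had SD 0.074. The variance is 0.0125 + 0.25 × 0.0055 = 0.0139, so SD = 0.118.
- In 600 simulated trials with minimum-P allocation, the planned model's mean standard error was 0.145 and the true SD 0.121. Type I error was 0.023, with Monte Carlo error √(0.023 × 0.977/600) = 0.006. A normal approximation agrees: 1.96 × 0.145/0.121 = 2.35, a two-sided tail of about 0.02.
- Power at d = 0.44 was 0.90 for the planned model and 0.96 with baseline adjustment. The normal approximation for the planned model is (0.44 − 1.96 × 0.145)/0.121 = 1.29, or 0.90.

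**5. Other allocation covariates.** In the planned model with complete data, a time-constant covariate leaves the standard error at 0.1443 whether it explains 0, 30% or 60% of the intercept variance. With baseline constrained, the standard error is 0.112, 0.105 and 0.095 respectively.

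**The case against.** The strongest reply is that nothing stated is wrong. The d = 0.44 at 80% power is reproduced, the error is on the safe side, and under the balancing allocation the planned model exceeds its power target. All of this stands.

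Four stronger readings are tempting, and the document does not support them.

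- *Omitting age, sex, baseline ISI and the other matching variables widens the standard error.* It does not. The contrast is within-person, so their main effects cancel (step 5). An article may also leave a covariate list to the analysis plan.
- *Power would rise from 81% to 96%.* That comparison is for 52 v 52 completers and ignores the allocation. With 60 v 60 the planned model has 0.86 even without the allocation, and 0.90 with it. The remaining gain is about 6 points.
- *The gain is large in any case.* It depends on an ICC given only as approximate, and it shrinks as the ICC rises.
- *Each of the four arms has its own baseline mean.* No CBT by CT term at baseline is listed, so read literally baseline is free by factor only.

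The reply does not remove the core. The article spells out the regressors of its primary model, and that list does not fit its own allocation.

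**Conclusion.** The point holds as a miscalibrated standard error and lost efficiency, not as bias or a wrong sample size. Under the described allocation the reported standard error is about 20% too large (0.145/0.121 = 1.20) and the test runs at about 2%. At ICC 0.50 the baseline fix cuts the model-based variance by 40% and raises power at d = 0.44 from about 0.90 to 0.96.

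This rests on an exchangeable correlation of 0.50, complete data in the simulation, other matching variables set as non-prognostic, and a deterministic choice of group after the initial simple randomization. At an ICC of 0.7 or 0.8 the saving in standard error is 13% or 8%. The change is worthwhile because the data are already collected, but the trial does not depend on it.

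**What to change.** Keep T0 as an outcome row, but drop the stand-alone CBT and CT terms. The fixed effects are then the intercept, time, follow-up, CBT by follow-up, CT by follow-up and CBT by CT by follow-up, with one common T0 mean. Enter the interaction columns directly, because a crossed model formula would restore the main effects. A common mean is justified by randomization and because T0 assessments are completed before participants learn their condition. This form keeps every randomized participant and costs no degrees of freedom.

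The alternative is to model T1-T4 IDS-SR with baseline IDS-SR as a covariate. It drops participants without any follow-up: at the planned 3% by T1, 0.03 × 120 = 3.6, or about four. The two forms are not identical. With a random intercept, the constrained form takes the baseline adjustment from the assumed equal variances and correlations, whereas the covariate form estimates it.

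Use the same approach for ISI, which is also a matching variable, and for other continuous outcomes measured at T0; the gain for these was not calculated.

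Optionally, after the baseline fix, add the main prognostic allocation covariates. If they explain an assumed 30% of the intercept variance, the standard error falls from 0.112 to 0.105, at the cost of a few degrees of freedom. The document gives no figure for their prognostic strength. No new data are needed, only a change of analysis wording before the condition codes are revealed.
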